#### 4. STUDY DESIGN

This is a multicentre, single-arm, phase 2 study according to Simon's two-stage optimal design. This design has been applied to minimize the number of patients exposed to a possibly inactive drug, considering that alternative treatment options exist, although not satisfactory and likely to be more toxic. Patients who will receive at least one dose of study drug will be considered evaluable.

The primary endpoint will be the rate of evaluable patients alive and not progressed at 6 months.

The sample size calculation is based on the following statistical parameters:

- minimum acceptable rate of patients alive without progression at 6 months ( $p_0$ ) = 30%;
- auspicated rate ( $p_1$ ) = 50%
- type I and II errors = 10%.

According to these parameters, 22 evaluable patients should be enrolled at the first stage and the study will proceed to the second stage if at least 8 patients will be alive without progression after 6 months. At the second stage, further 24 evaluable patients will be enrolled for an overall sample of 46 evaluable patients. The study will be considered positive if at least 18 patients out of 46 will be alive without progression at 6 months. It is planned that 5 to 10 centres will participate in the study, which could be completed in 24 months.

## 5. TREATMENT PLAN

### 5.1. Regorafenib treatment

Patients will receive regorafenib orally 160 mg once daily for the first 3 weeks of each 4-week cycle.

Treatment will be definitively stopped in case of disease progression, unacceptable toxic effects, motivated decision to stop the treatment by the treating physician, or refusal or withdrawal of consent by the patient.

### 5.2 Dose modifications and interruptions

The dose or dosing schedule of the study drug may be modified following the occurrence of a clinically significant AE that is:

- related or not related to the study drug, and
- of a pre-specified severity Grade

All dose modifications are to be made according to the pre-defined dose levels presented in Table 1.

**Table1 : Pre-defined dose levels**

| Dose level                   | Number of tablets                    |
|------------------------------|--------------------------------------|
| Dose level 0 (standard dose) | 4 regorafenib 40-mg tablets (160 mg) |
| Dose level -1                | 3 regorafenib 40-mg tablets (120 mg) |
| Dose level -2                | 2 regorafenib 40-mg tablets (80 mg)  |

Dose reductions leading to a daily dose below Dose Level -2 (ie, fewer than 2 tablets daily) are not permitted. Treatment will be definitively discontinued if the subject is unable to tolerate a daily dose of at least two tablets.

Treatment with the study drug will be also definitively discontinued if it is necessary to interrupt the study drug treatment schedule for more than one cycle (4 consecutive weeks that is maximum of 5 weeks permitted between doses of regorafenib).

#### 5.2.1. Recommended dose modifications

Recommended dose modifications (dose reduction and dose interruption) for general and special situations are provided in Table2, Table3, Table4 and Table5.

### 5.2.2. Conflicting recommendations for dose modification

A subject may simultaneously experience several clinically significant toxicities requiring dose modification. If the recommendations for dose modification related to the simultaneously experienced toxicities conflict with one another, the investigator should select the dose modification resulting in the lowest dose level.

### 5.2.3. Dose re-escalation

The maximum dose level is 0 (4 tablets daily). If dose reduction is required to Dose Level -1 (3 tablets daily) or Dose Level -2 (2 tablets daily), the dose may be re-escalated (increased) to Dose Level -1 (3 tablets daily) or Dose Level 0 (4 tablets daily) at the discretion of the investigator, provided the severity of all AEs requiring dose reduction have returned to baseline Grades after a full cycle of therapy. Dose escalation should be done one dose level at a time.

The exception to this rule occurs with toxicities associated with HFSR, also known as PPE. For subjects with HFSR, dose re-escalation may be considered, at the discretion of the investigator, after AE severity is reduced to Grade  $\leq 1$ . Additional details are provided below (*Dose modifications and supportive measures for HFSR*) and in Table 3.

### 5.2.4. Dose modifications: general and special recommendations

#### General recommendations

Recommended dose modifications are shown in Table 2 for any clinically significant toxicity that:

- is considered to be related to the study drug,
- has a severity grade  $\geq 3$  (as defined in NCI-CTCAE v 4.0), and
- is not covered by a special recommendation.
- in addition to the recommended dose modifications, subjects who develop diarrhea, mucositis, anorexia or other events predisposing to fluid loss or inadequate fluid intake should be carefully monitored and rehydrated as clinically necessary to minimize the risk of postural hypotension and renal failure.

#### Special recommendations

- Recommended dose modifications for HFSR (PPE syndrome) with severity Grade  $\geq 1$  are provided in Table 3.
- Required dose modifications for ALT and/or AST increases related to study drug with severity Grade  $\geq 1$  (CTCAE v 4.0) are provided in Table 4; recommended liver function monitoring schedules are also provided.
- Recommended dose modifications for treatment-emergent hypertension with severity Grade  $\geq 1$  (CTCAE v 4.0) are provided in Table 5; general recommendations for the management of hypertension are also provided.

### 5.2.5. Dose modification/interruption for AEs related to the study drug (except HFSR, hypertension, and liver function test abnormalities)

As shown in Table 2, a study drug-related Grade 3 toxicity (except HFSR, hypertension, and liver function test abnormalities) requires interruption of dosing until the toxicity severity is reduced to  $\leq$  Grade 2. Treatment is then to be restarted at the dose level immediately below the original dose level. If the toxicity severity returns to baseline, dose escalation may be considered at the discretion of the investigator. A second occurrence of an AE with a severity of Grade 3 requires a permanent reduction of dose level. An AE with a severity of Grade 4 requires dose interruption until the severity is reduced to  $\leq$  Grade 2 and a permanent dose reduction of one dose level. All dermatological AEs, except for HFSR, should be managed according to the guidelines in Table 2.

**Table 2: Dose modification/interruption for adverse events related to the study drug\* (except hand-foot skin reaction, hypertension, and liver function test abnormalities)**

| Severity Grade (CTCAE v 4.0) | Dose Interruption                       | Dose Reduction                                                                                        | Dose for Subsequent Cycles                                                                                                                                                                                                 |
|------------------------------|-----------------------------------------|-------------------------------------------------------------------------------------------------------|----------------------------------------------------------------------------------------------------------------------------------------------------------------------------------------------------------------------------|
| Grade 0-2                    | Treat on time                           | No change                                                                                             | No change                                                                                                                                                                                                                  |
| Grade 3                      | Delay until $\leq$ Grade 2 a | Reduce by 1 dose level                                                                                | If toxicity remains $\leq$ Grade 2, dose re-escalation may be considered at the discretion of the treating investigator. If dose is re-escalated and toxicity ( $\geq$ Grade 3) recurs, institute permanent dose reduction |
| Grade 4                      | Delay until $\leq$ Grade 2 a | Reduce by 1 dose level. Permanent discontinuation may be considered at the investigator's discretion. | ---                                                                                                                                                                                                                        |

\* Excludes alopecia, non-refractory nausea/vomiting, non-refractory hypersensitivity, and non-clinically significant and asymptomatic laboratory abnormalities

a: If no recovery after one cycle (4 consecutive weeks; maximum of 5 weeks between doses of regorafenib), treatment should be permanently discontinued.

### 5.2.6. Dose modifications and supportive measures for HFSR

Prior to beginning treatment with study drug, measures that may prevent or minimize the severity of HFSR should be undertaken. If HFSR of severity Grades 1 or 2 occurs during treatment, any preventive or supportive measures not already taken should be instituted immediately. These include the following:

#### 1. Control of calluses

Before initiating treatment with the study drug:

- Check condition of hands and feet.
- Suggest a manicure/pedicure, when indicated.
- Recommend pumice stone use for callus or “rough spot” removal.
- During regorafenib treatment:
- Avoid pressure points.
- Avoid items that rub, pinch, or create friction.

#### 2. Use of creams

- Non-urea-based creams: apply liberally
- Keratolytic creams: use sparingly and apply only to affected (hyperkeratotic) areas.
- Urea-based creams
- Salicylic acid 6%
- Alpha hydroxy acid-based creams
  - Creams containing approximately 5% to 8% alpha hydroxyl acid provide gentle chemical exfoliation.
  - Apply liberally twice daily.
- Topical analgesics, such as lidocaine 2%, should be considered for pain control.
- High-potency topical corticosteroids, such as clobetasol 0.05%, should be considered for subjects with HFSR Grade 2 or 3. Avoid systemic steroids.

#### 3. Cushions

Protect tender areas:

- Use socks/gloves to cover moisturizing creams.
- Wear well-padded footwear.
- Use insole cushions or inserts (eg, silicon, gel).
- Foot soaks with tepid water and Epsom salts

If supportive measures do not produce the desired effects, dose modification, as outlined in Table 3, is the next step. Dose interruption (7 days) followed by

restarting treatment at Dose Level -1 may be instituted for Grade 2 toxicity if supportive measures do not reduce the severity to  $\leq$  Grade 1 within 7 days.

For subjects with Grade 3 HFSR, at the first occurrence a 1-level dose reduction is recommended; at the second occurrence a decrease of an additional dose level is recommended.

Study treatment is to be discontinued for the fourth occurrence of HFSR Grade 2 and for the third occurrence of HFSR Grade 3.

For subjects who require a dose reduction for Grade 2 or 3 HFSR, the dose of study drug may be increased to the starting dose after one full cycle of therapy has been administered at the reduced dose without the appearance of HFSR  $>$  Grade 1. Dose escalation should be done one dose level at a time.

In general, a more liberal management for dose modification is allowed if judged by the investigator to be medically appropriate (eg, dose reduction for Grade 1 HFSR).

**Table 3: Dose modification/interruption and toxicity grading for hand-foot skin reaction (palmar-plantar erythrodysesthesia syndrome)**

| Skin Toxicity Grade (CTCAE v 4.0)                                                                                                                                            | Occurrence                                 | Suggested Dose Modification/Interruption a                                                                                                                    |
|------------------------------------------------------------------------------------------------------------------------------------------------------------------------------|--------------------------------------------|--------------------------------------------------------------------------------------------------------------------------------------------------------------------------|
| Grade 1: Numbness, dysesthesia, paraesthesia, tingling, painless swelling, erythema or discomfort of the hands or feet that does not disrupt the subject's normal activities | Any                                        | Maintain dose level and institute supportive measures immediately for symptomatic relief.                                                                                |
| Grade 2: Painful erythema and swelling of the hands or feet and/or discomfort that affects the subject's normal activities                                                   | 1st occurrence                             | Institute supportive measures immediately. Consider decreasing dose by one dose level; if no improvement, interrupt therapy for 7 days or until toxicity $\leq$ Grade 1. |
|                                                                                                                                                                              | No improvement at 7 days or 2nd occurrence | Interrupt therapy $\leq$ 28 days a or until toxicity $\leq$ Grade 1. When resuming treatment, reduce dose by one dose level.                                  |
|                                                                                                                                                                              | 3rd occurrence                             | Interrupt therapy $\leq$ 28 days a or until toxicity $\leq$ Grade 1. When resuming treatment, reduce dose by one additional dose level. b,c        |
|                                                                                                                                                                              | 4th occurrence                             | Discontinue treatment                                                                                                                                                    |

**Table 3: Dose modification/interruption and toxicity grading for hand-foot skin reaction (palmar-plantar erythrodysesthesia syndrome)**

| Skin Toxicity Grade (CTCAE v 4.0)                                                                                                                                                                | Occurrence     | Suggested Dose Modification/Interruption a                                                                                                                                                                                      |
|--------------------------------------------------------------------------------------------------------------------------------------------------------------------------------------------------|----------------|--------------------------------------------------------------------------------------------------------------------------------------------------------------------------------------------------------------------------------------------|
| Grade 3: Moist desquamation, ulceration, blistering or severe pain of the hands or feet, or severe discomfort that causes the subject to be unable to work or perform activities of daily living | 1st occurrence | Institute supportive measures immediately. Interrupt therapy for 7 days or until toxicity $\leq$ Grade 1. When resuming treatment, decrease dose by one dose level. c                                                           |
|                                                                                                                                                                                                  | 2nd occurrence | Institute supportive measures immediately. Interrupt therapy for a minimum of 7 days but $\leq$ 28 days a or until toxicity $\leq$ Grade 1. When resuming treatment, decrease dose by one additional dose level. b,c |
|                                                                                                                                                                                                  | 3rd occurrence | Discontinue treatment permanently.                                                                                                                                                                                                         |

In general, a more liberal management for dose modification is allowed if judged by the investigator to be medically appropriate (eg, dose reduction for Grade 1 hand-foot skin reaction).

- Dose interruption for  $\geq$  28 days (one cycle [4 consecutive weeks; maximum of 5 weeks between doses of regorafenib]) requires permanent discontinuation of study drug.
- The lowest recommended dose is 80 mg.
- If toxicity  $\leq$  Grade 1 after dose reduction for one full cycle of therapy, dose re-escalation is permitted at the investigator's discretion.

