- Subjects requiring a delay of study treatment > one cycle (4 consecutive weeks; maximum of 5 weeks between doses of regorafenib) must discontinue study drug.
- If BP remains controlled for ≥ one full cycle, dose re-escalation is permitted at the investigator's discretion.
- Subjects requiring dose reduction below Dose Level -2 (80mg) must discontinue study drug.

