### 5.3. Definitive interruption of study treatment

A subject can definitively interrupt study treatment for the following reasons:

- Unequivocal progression of disease as demonstrated on a CT/MRI scan. In the case of equivocal lesions, subjects should continue to receive study drug until progression is confirmed (CT/MRI scan, follow-up).
- If, in the investigator's opinion, continuation in the study would be harmful to the subject's well-being
- At his/her own request or at the request of his/her legally acceptable representative. At any time during study treatment and without giving a reason, a subject or his/her legally acceptable representative may decline further study treatment. The subject will not suffer any disadvantage as a result. The subject will continue to be followed up for safety and survival unless he/she withdraws consent.
- Study drug dose reduction by more than two dose levels
- Study drug dose interruption for more than one cycle (4 consecutive weeks; maximum of 5 weeks between doses of regorafenib)
- Severe allergic reactions, such as exfoliate erythroderma, anaphylaxis, or vascular collapse
- Any other adverse reaction deemed sufficiently serious to warrant discontinuation of treatment by the investigator
- If female, a pregnancy test result consistent with pregnancy
- Use of illicit drugs or other substances that may, in the opinion of the investigator, have a reasonable chance of contributing to toxicity or otherwise confounding the results of the study
- Development of any intercurrent illness or situation that may, in the judgment of the investigator affect assessments of clinical status and study endpoints to a relevant degree
- Development of a second malignancy except for cervical cancer in situ, nonmelanoma skin cancer, or superficial bladder tumors classified as noninvasive tumor (Ta), carcinoma in situ (Tis), or tumor invades lamina propria (T1).
- Any subject who definitively interrupt study treatment will be evaluated at the End-of-treatment Visit conducted 30 days ( $\pm 7$  days) after permanently stopping study treatment.
- In all cases, the reason for definitive interruption of study treatment must be entered in the electronic Case Report Form (eCRF) and in the subject's medical records.

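### Table 3 joins hold time and recovery with 'or' for Grade 3 hand-foot skin reaction, so read literally it permits restart without recovery; its row and footnote also conflict at exactly day 28 (minor safety wording)

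*Protocol*

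**What the plan says.** Table 3 gives two interruption rules for Grade 3 HFSR.

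- First occurrence: "Interrupt therapy for 7 days or until toxicity $\leq$ Grade 1. When resuming treatment, decrease dose by one dose level".
- Second occurrence: "Interrupt therapy for a minimum of 7 days but $\leq$ 28 days", followed by the same 'or' alternative of recovery to Grade 1 or lower. The dose then falls by one further level.

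A third Grade 3 occurrence ends treatment.

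The second-occurrence time range carries a marker to a footnote, under which "Dose interruption for $\geq$ 28 days" means permanent discontinuation. The general limit elsewhere is worded differently:

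- Section 5.2 discontinues "if it is necessary to interrupt the study drug treatment schedule for more than one cycle".
- Section 5.3 lists "Study drug dose interruption for more than one cycle".
- The Table 5 footnote applies to "Subjects requiring a delay of study treatment > one cycle".

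All three define a cycle as four consecutive weeks.

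**The concern.** An 'or' between a fixed time and a recovery condition means that either one is enough. If elapsed time is enough, the recovery condition does not protect the patient who needs it, namely the one who has not improved. Table 3 defines Grade 3 HFSR by moist desquamation, ulceration, blistering or severe pain. A site following the row to the letter could give regorafenib again on day 7 to a patient in that state, at a reduced dose.

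The day-28 boundary is a separate matter. It decides whether a patient who recovers on that day resumes treatment or leaves it for good, and the protocol gives both answers.

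**Working it through.** No sample size, error rate or event count enters this point. The check is a reading of the rules side by side, with simple day counts.

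**1. What each Grade 3 row permits, read literally**

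| Case | Condition met | Result |
|---|---|---|
| 1st occurrence, still Grade 3 on day 7 | 7 days elapsed | restart one level lower |
| 2nd occurrence, still Grade 3 on day 7 | hold within 7 to 28 days | restart one further level lower |
| 2nd occurrence, recovered on day 3 | Grade 1 or lower reached | restart on day 3, before the 7-day minimum |

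With the dose levels in Table 1, and assuming a patient who starts at 160 mg and is not re-escalated, the first restart is at 120 mg and the second at 80 mg.

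**2. Does any other text require recovery first?**

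- Section 5.2.6, running text: for Grade 3 it gives the dose reductions and the third-occurrence stop, but no grade that must be reached before restart.
- Section 5.2.3 and the Table 3 re-escalation footnote: both require Grade 1 or lower, but for raising the dose again, not for restarting after a hold.
- Table 2: requires recovery, but excludes HFSR by its title and by section 5.2.5.
- Section 5.3: lets the investigator stop treatment that would be harmful, but sets no restart condition.

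None of these closes the gap.

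**3. The Grade 3 rules for other toxicities**

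- Table 2 (other drug-related events): "Delay until $\leq$ Grade 2", with permanent discontinuation if there is no recovery after one cycle.
- Table 4 (ALT/AST): dosing stays interrupted until transaminases fall below 3 × ULN or return to baseline.
- Table 5 (hypertension): dosing is delayed until diastolic pressure is at most 90 mmHg and any symptoms have resolved.

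All three make recovery a condition for restart. The Table 3 discontinuation footnote is triggered only by the length of the interruption, so a restart on day 7 never reaches it.

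**4. A hold of exactly 28 days**

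| Provision | Limit | Day 28 |
|---|---|---|
| Table 3, Grade 3, 2nd occurrence | at most 28 days | may resume |
| Section 5.2 | more than one cycle (4 weeks) | may resume |
| Section 5.3 | more than one cycle | may resume |
| Table 5 footnote | more than one cycle | may resume |
| Table 3 footnote | 28 days or more | must discontinue |

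The conflict does not depend on how 'or' is read. A 28-day hold plus the scheduled 7-day rest is 28 + 7 = 35 days, which equals the stated maximum of 5 weeks between doses. That fits the four provisions that allow day 28.

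**5. Extra time off drug if recovery is required**

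- If a 28-day hold is allowed: 28 − 7 = 21 further days at most.
- If the footnote's limit governs, so that 27 days is the longest hold: 27 − 7 = 20 further days at most.
- Recovery on day 3 at a first occurrence, with a 7-day minimum: 7 − 3 = 4 days' wait.

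**The case against.** The strongest reply is that the rows were meant as whichever is later. The second-occurrence row sets a minimum and a maximum, and that range makes best sense if recovery decides when, within it, the hold ends. The clause about resuming fixes the dose, not the day, and neither row obliges anyone to restart a patient who is still at Grade 3. This is probably the intent, but the text does not say so. On that reading the 28-day figure also no longer limits the hold within the row, and only the footnote does. The row needs rewording either way.

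Second, Table 3 is headed as suggested, and investigators may manage differently where medically appropriate. Section 5.3 allows treatment to be stopped, every Grade 3 restart is at a lower dose, and a third occurrence ends treatment. These safeguards stand and limit the weight of the point. They do not tell a site what the default rule is, nor do they settle a footnote worded as a requirement.

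Third, section 5.2.6 expressly allows a 7-day interruption followed by a restart at Dose Level −1 for Grade 2 reactions that supportive measures have not brought down. That weakens the comparison with Tables 2, 4 and 5, although it covers Grade 2 only. It also shows that a site could plausibly read the Grade 3 figure of 7 days as a fixed hold.

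A reader might go further and infer that Grade 3 patients are less protected than Grade 2 patients, because Grade 2 has a row headed "No improvement at 7 days or 2nd occurrence" and Grade 3 has none. The document does not support that. The Grade 2 row joins its time limit to recovery with the same 'or', so read literally it does not require recovery either.

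**Conclusion.** The point holds as a minor safety wording error with two parts. Both Grade 3 interruption rows (2 of 2) let elapsed time alone end the hold if read literally, and no other text requires recovery first. The Grade 3 rules in the other three tables (3 of 3) do require it. Separately, a hold of exactly 28 days is both permitted and prohibited.

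The first part rests on the literal reading. The second does not, but it concerns a single day. The protocol gives no rate of Grade 3 HFSR, so the number of patients affected cannot be estimated; the 20 or 21 days are differences between limits, not a measure of harm.

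A reader might infer that the protocol directs sites to re-dose unhealed skin, or that the primary result is at risk. Neither follows. The rows permit a restart but do not order one, and the event rule in section 9.1 is the same under either reading.

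**What to change.** In both Grade 3 rows of Table 3, replace the interruption rule with: *Interrupt therapy for at least 7 days and until toxicity ≤ Grade 1; if not recovered by day 28 of the interruption, discontinue permanently.* Keep the existing supportive measures and dose reductions: one level at the first occurrence, one additional level at the second. Change the Table 3 footnote from 28 days or more to more than 28 days, so that it agrees with its own row, with sections 5.2 and 5.3 and with the Table 5 footnote.

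The edit touches two rows and one footnote and adds no visits or patients. Some patients will stay off drug longer, by up to 21 days, or will be discontinued under the existing cap. A first-occurrence patient who recovers early waits until day 7. On the footnote, the edit adopts the looser of the two day-28 limits, because that is the one the rest of the protocol uses. The Grade 2 rows keep their 'or'; they are left out of this edit because section 5.2.6 expressly describes the 7-day hold and restart for Grade 2.
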